## Abstract

**Introduction:**

Around 140 million children are born every year and post-natal transition is uncomplicated in the vast majority. However, around 5%–15% of neonates receive supportive interventions during transition. Recent data on the interventions used is scarce. More data on the frequencies with which these interventions are used is needed to evaluate neonatal resuscitation, guide recommendations and to generate hypotheses for further research. The following protocol describes an international, multicentre survey on the interventions currently applied during neonatal resuscitation.

**Objectives:**

To determine the frequencies at which different supportive interventions recommended by European Resuscitation Council (ERC) guidelines for neonatal resuscitation are used. To compare the frequencies between hospitals and patient groups and to investigate possible factors influencing any differences found.

**Methods:**

Participating hospitals will collect data on all interventions performed during neonatal resuscitation over a period of 6 months. All hospitals providing perinatal care are eligible regardless of size and designated level of neonatal care. Every neonate requiring more interventions than basic drying and tactile stimulation during the first 30 min of life will be included. The targeted sample size is at least 4,000 neonates who receive interventions. After anonymization, the data is pooled in a common database and descriptive and statistical analysis is performed globally and in subgroups. Possible correlations will be investigated with phi coefficient and chi square testing.

**Ethics and dissemination:**

Consent of the institutional review board of the Technical University Dresden was obtained for the local data collection under the number BO-EK-198042022. Additionally, approval of local ethical or institutional review boards will be obtained by the participating hospitals if required. Results will be published in peer-reviewed journals and presented at suitable scientific conferences.

## Introduction

The transition to extra-uterine life is the most complex adaptation in life, involving major cardiorespiratory, hemodynamic and metabolic changes (1, 2). The majority of infants undergo this transition without any problems. However, it is estimated that up to 16% of newborns receive supportive interventions in the delivery room (DR) (3–5). With around 140 million births per year worldwide, this makes neonatal resuscitation and support of transition one of the most frequently performed medical interventions (6, 7).

The published frequency of medical interventions in the DR is based on limited data which are more than 20 years old (3, 8, 9). More recent data were mostly obtained from single centres in a certain region and do not take into account important risk factors like gestational age or mode of birth (10–14). Therefore, more current data on the frequency of DR-interventions are urgently needed, reflecting not only different national health systems and levels of care but also accounting for certain risk factors.

We aim to describe current practice in postnatal support by prospectively surveying clinicians at many hospitals internationally. Information will be collected on each DR-intervention that is performed at each participating centre for a period of 6 months. The data will be analysed regarding possible influencing factors both patient specific (e.g., gestational age, mode of birth) and structural (e.g., level of neonatal care, centre size).

### Objectives

The overall aim of this survey is to estimate the frequency of various interventions applied to newborn infants in the DR and to investigate the impact of possible influencing factors such as centre size and location, level of neonatal care, working hours and weekly periods.

The main objectives of this study are:
1.To estimate the total frequency of interventions given to neonates in the DR in order to support neonatal transition and to compare this estimate with prior data.2.To estimate the frequency of single supportive interventions applied to neonates in the DR.3.To investigate the impact of the following patient-specific factors on supportive interventions:
a.gestational age (separated into different gestational age groups)b.mode of birth (c-section vs. vaginal delivery)4.To investigate the impact of the following structural factors on frequency of single interventions:
a.Designated level of neonatal care according to the definition of the American Academy of Pediatrics (AAP) (15)b.Centre size (defined by total number of newborn infants in 2021)c.Presence of trained neonatologists 24/7d.Centre location (defined by country)5.To investigate the impact of the following organisational factors on frequency of supportive interventions:
a.Weekly period of birth (Monday–Friday vs. weekend)b.Daily period of birth (00.00–08.00, 08.00–16.00, 16.00–00.00)Further objectives include:
6.To further elucidate the mode of respiratory support by analysing the combined frequency of the use of CPAP, non-invasive ventilation and invasive ventilation, and by analysing the frequency of primary intubation (without application of non-invasive respiratory support).7.To generate current data regarding surfactant administration in the DR by comparing the frequency of less-invasive surfactant administration versus application *via* endotracheal tube.8.To investigate the frequency of laryngeal mask use as an alternative airway management tool in the DR.9.To further elucidate the current practice regarding the route of drug administration by comparing the frequency of peripheral venous, umbilical venous and intra-osseous access in the DR.10.To evaluate certain indicators of adherence to ERC guidelines (e.g., oxygen supplementation in resuscitation of early pre-term infants).

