### Study variables

For every included neonate the following data are collected:
•Weekly period of birth (Mo–Fr/Weekend)•Time period of birth (8:00–16:00/16:00–0:00/0:00–8:00)•Completed week of gestation•Mode of birth (c-section/no c-section)•Application of the following items during neonatal resuscitation:
○Respiratory support:
◾ Initial inflations◾ CPAP◾ Non-invasive ventilation◾ Oxygen supplementation○Airway management:
◾ Suction*◾ Laryngeal mask◾ Endotracheal intubation + invasive ventilation○Drug application:
◾ Surfactant administration (*via* endotracheal tube)◾ Less-invasive Surfactant administration (LISA)◾ adrenaline◾ Caffeine○Vascular access
◾ Peripheral IV access*◾ Umbilical venous access◾ Intraosseous access○Chest compressions (if performed at least once)Marked items (*) will only be recorded if performed together with other interventions due to practicability aspects. Tactile stimulation is not recorded because while it is most likely applied to every neonate, the management varies widely between centres and there exists no consensus on the most effective stimulation method (16).

For detailed definitions of the variables see Table 1.

**Table 1 T1:** Definitions of study variables/data collection form items.

Study variable	Definition
Initial inflations	Positive pressure application using a facemask (at least ≥10 cm H_2_O over PEEP) over at least 2 s at least once before any other respiratory support
CPAP	Continuous positive pressure application (≥5 cm H_2_O) with sufficient device positioning and regardless of interface and pressure driver
Non-invasive ventilation	Intermittent positive pressure ventilation (iPPV) at least two times in a row regardless of interface and pressure driver; initial inflations excluded
Suction	Use of any suction device for airway clearance
Laryngeal mask	Insertion of laryngeal mask as airway device
Oxygen supplementation	Application of any additional oxygen, FiO_2_ > 0.21
Intubation + invasive ventilation	Ventilation *via* endotracheal tube (ETT); not to be ticked if intubation was used as mean for surfactant administration and the infant was extubated prior to the end of neonatal resuscitation
Surfactant *via* ETT	Surfactant administration *via* endotracheal tube, regardless of continuation of invasive ventilation after Surfactant administration
Less-invasive surfactant administration	Any other form of Surfactant administration less invasive than *via* endotracheal tube

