### Data analysis

Data will be analysed globally and for specific, predefined subgroups for every independent variable (e.g., completed week of gestational age, mode of birth, designated level of neonatal care).

Descriptive analysis will be performed on all study variables including absolute numbers and percentages as well as median and range for numerical variables. For all observed interventions confidence intervals will be calculated on a confidence level of 0.95. Additionally, statistical analysis regarding possible correlations will be performed on all study variables using phi coefficient and chi square test of independence. Statistical analyses and graphical presentations will be performed using R (The R Foundation for Statistical Computing, Vienna, Austria).

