## Anticipated results

We are expecting that the targeted sample size of at least 4,000 neonates receiving interventions will be collected within 1 year of enrolling the first hospital. To reduce bias, we are looking to collect data on equal amounts of births for every level of neonatal care and to include a hospital of every level of neonatal care from every participating country.

The minimum of anticipated results of descriptive and statistical analysis is listed in Table 2. Further results of additional analysis might be added if the need emerges during the data analysis process. Selected results of descriptive analysis and significant statistical analysis will be presented in graphical form as diagrams. All results regardless of significance will be presented in tabular form, at the least as supplementary material of the planned publication.

**Table 2 T2:** List of anticipated results of descriptive and statistical analysis.

Descriptive analysis	Statistical analysis
Total intervention frequency (global and stratified into subgroups sorted by mode of birth, level of neonatal care, center size, country, weekly period of birth, daily period of birth)	Significant differences in total intervention frequency between the stratified subgroups (mode of birth, level of neonatal care, center size, country, weekly period of birth, daily period of birth)
Frequency of single supportive interventions (global and stratified into subgroups sorted by gestational age, mode of birth, level of neonatal care, center size, country, weekly period of birth, daily period of birth)	Significant differences in single supportive intervention frequency between the stratified subgroups (mode of birth, level of neonatal care, center size, country, weekly period of birth, daily period of birth)
Combined frequency of CPAP, non-invasive ventilation and invasive ventilation and frequency of primary intubation (without application of non-invasive respiratory support)	Significant differences in single supportive intervention frequency for neonates receiving interventions stratified by gestational age groups

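### Objectives 4 and 5 ask for the impact of structural and organisational factors, but the only tests named are unadjusted, so differences in gestational age and mode of birth can appear as differences by level, size, country or time

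*Protocol article*

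**What the plan says.** Under Objectives, objective 4 is "To investigate the impact of the following structural factors on frequency of single interventions"; the factors are level of care, centre size, round-the-clock neonatologist presence and country. Objective 5 is "To investigate the impact of the following organisational factors on frequency of supportive interventions", meaning weekday against weekend and three eight-hour periods.

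The Data analysis section names one inferential approach: "statistical analysis regarding possible correlations will be performed on all study variables using phi coefficient and chi square test of independence". The abstract names the same two methods. On subgroups it says "Data will be analysed globally and for specific, predefined subgroups for every independent variable".

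Table 2 (Anticipated results) promises "Significant differences in single supportive intervention frequency between the stratified subgroups (mode of birth, level of neonatal care, center size, country", followed by the two time factors. Gestational age has its own row in the statistical column, restricted to treated infants, and is not crossed with any structural or organisational factor.

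The Introduction faults recent data because they "do not take into account important risk factors like gestational age or mode of birth". Study variables lists completed week of gestation and mode of birth under the lead-in "For every included neonate the following data are collected".

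**The concern.** A chi-square test of an intervention against level of care compares whatever infants each level happened to treat. If one level treats more very preterm infants, and very preterm infants receive the intervention more often, the levels will differ even if every hospital would treat a given infant identically. The same applies to centre size and country. It also applies to time of birth if the share of c-sections varies over the week or day.

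A larger sample does not remove such a difference; it only makes it more significant. Objectives 4 and 5 are where this matters. The global frequencies under objectives 1 and 2 are unaffected.

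**Working it through.** **The plan's own figures.** The sample-size chain reproduces exactly:

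- 20 / 0.0005 = 40,000 births
- 40,000 / 500 = 80 hospitals
- 40,000 × 0.10 = 4,000 treated infants

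The chain is built on a count of adrenaline recipients. No power calculation is given for any comparison, so there is none to reproduce.

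**What the documents allow.**

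| Analysis | Gestational age | Mode of birth |
|---|---|---|
| Single interventions among included infants | recorded per infant | recorded per infant |
| Frequency per birth, site-level factors | no denominator listed | monthly c-section births per site |
| Frequency per birth, weekday or hour | no denominator listed | no denominator by weekday or hour listed |

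Full adjustment is therefore possible only in the first row.

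**Illustration 1: size of a spurious difference.** All inputs are assumptions; none comes from the documents. Intubation risk among treated infants is the same at every level: 60% below 28 weeks, 25% at 28–31, 5% at 32–36 and 3% at 37 or more. The treated mix over these bands is 0/1/14/85% at level I and 8/12/30/50% at level IV. Crude frequency is the sum of share × risk:

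- Level I: 0 × 0.60 + 0.01 × 0.25 + 0.14 × 0.05 + 0.85 × 0.03 = 0.0025 + 0.0070 + 0.0255 = 0.035
- Level IV: 0.08 × 0.60 + 0.12 × 0.25 + 0.30 × 0.05 + 0.50 × 0.03 = 0.048 + 0.030 + 0.015 + 0.015 = 0.108
- Ratio: 0.108 / 0.035 = 3.1

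Within each band the ratio is 1 by construction, so stratifying removes the whole difference.

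**Illustration 2: how often the planned test would reject.** The assumptions are four levels with 1,000 treated infants each, an intervention risk that depends only on being very preterm, no level effect, two-sided 5% tests and 2,000 simulations per scenario. The crude 4 × 2 chi-square is compared with a generalised Cochran–Mantel–Haenszel (CMH) test stratified by very preterm status. The odds ratio is crude, highest against lowest level.

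| Very preterm share by level | Risk, very preterm / other | Crude odds ratio | Crude test rejects | CMH rejects |
|---|---|---|---|---|
| 5/5/5/5% | 30% / 5% | 1.00 | 5% | 5% |
| 2/3/4/5% | 20% / 10% | 1.03 | 5% | 5% |
| 2/5/10/15% | 30% / 5% | 1.65 | 74% | 5% |
| 1/5/15/30% | 50% / 5% | 3.94 | 100% | 6% |

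The odds ratio in the third row is (0.0875/0.9125) / (0.055/0.945) = 1.65. Over all nine unequal-mix scenarios run, the crude test rejected in 5% to 100% and the stratified test in about 4% to 6%.

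**Room for hospital-level factors.** The Sample size section aims for 20 countries and ideally four hospitals in each, one per level: 80 / 20 = 4 per country, or one hospital per country-and-level cell.

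**The case against.** The strongest defence is that this is a descriptive survey reported in a condensed article. Table 2 is described as a minimum, further analyses may be added, and subgroup analysis by completed week is mentioned. The Discussion says that no causal relationships can be analysed. Crude frequencies by level or country are legitimate descriptive results, and model covariates are commonly left to an analysis plan.

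Part of this stands. The absence of a regression model would not by itself be a fault. But the article does not leave the method open: it names the tests and lists the comparisons, and these do not fit the objectives. Additions made if the need emerges during analysis are not prespecified. The limitations paragraph names only unrecorded confounders (indication, maternal characteristics) and not the two that are recorded. Seeking equal numbers of births per level balances counts, not case-mix.

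A reader might infer more than the documents support:

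- **That case-mix will be reported as a causal structural effect.** The causality caveat speaks against this. The risk is that differences are read that way.
- **That objective 3 fails in the same way.** It studies gestational age and mode of birth themselves, so it cannot misattribute gestational-age mix to level, size, country or hours.
- **That the hospital benchmarking will be confounded.** Only comparison with the global dataset is announced, and no method is given.
- **That adjustment solves everything.** Infants enter only if treated. A hospital that gives brief CPAP freely dilutes its own intubation percentage, and adjusting for gestational age does not undo that.

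**Conclusion.** The point holds for objectives 4 and 5. The stated method cannot separate structural or organisational differences from differences in the infants treated, although the data to do so in part are being collected and the Introduction presents this as the gap to fill.

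The size is unknown. The documents give neither a gestational-age mix by level nor intervention risks by gestational age. The 3.1-fold figure is one illustration, for one intervention with an assumed steep gradient in gestational age. It is not an estimate for this survey and does not carry over to oxygen, CPAP or initial inflations. With similar case-mix or a shallow gradient the bias is negligible (crude odds ratio 1.03); with strong imbalance it dominates (3.94). That higher levels treat more preterm infants, or that c-sections cluster in working hours, is plausible but is an assumption here.

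**What to change.** 1. Keep the crude tables and label them descriptive.
2. For single interventions among included infants, make results stratified by or adjusted for gestational age and mode of birth the main analysis for objectives 4 and 5. Stratified Mantel–Haenszel or logistic regression would serve, with allowance for clustering by hospital (a random hospital effect or cluster-robust errors).
3. Examine level, size, neonatologist presence and country in sparse models. With about one hospital per country-and-level cell, they cannot all be separated well.
4. Use penalised or purely descriptive analysis for rare items; the design aims for as few as 20 adrenaline recipients.
5. For total frequency per birth, stratify the site-level comparisons by mode of birth, using the monthly c-section counts.
6. State three limits: gestational age cannot be adjusted for per birth; no birth denominator by weekday or time of day is listed; and estimates among treated infants are conditional on each hospital's threshold for treating.
7. Replace *impact* with *association* in the objectives.

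For items 1 to 7 no new data are needed. Per-birth comparisons by weekday or hour would need denominators that are not listed. The cost is somewhat more analysis work, and adjusted estimates for rare interventions and for country will be imprecise.

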## Methods and analysis

### Study design

The study is an international, prospective and observational multi-centre survey. Anonymous data on interventions administered in the DR will be acquired once per patient. Follow-up data collection on the included patients is not planned.

### Study population/inclusion and exclusion criteria

Supportive DR-interventions are surveyed for all neonates who fulfil the following criteria:
◾ born in a participating hospital during the 6-month survey period◾ receive supportive interventions more than basic drying or tactile stimulation during the first 30 min of lifeNeonates are excluded based on the following criteria:
◾ neonates receiving only suction or peripheral venous access without any other supportive intervention◾ neonates requiring supportive interventions only after the first 30 min of life.

### Sample size

The targeted sample size was decided upon empirically. The rarest described intervention in the literature is the administration of epinephrine with a frequency of as low as 0.05% and we wanted to collect data on at least 20 infants receiving this intervention. Therefore, the calculated total number of births during the study period must equal or exceed 40,000. We expect at least 500 births per participating hospital during the study period, leading to a target of 80 participating hospitals. Assuming an intervention rate of 10%, this results in a sample size of 4,000 infants receiving interventions. As we wish to be able to strive to have meaningful comparisons between different levels of neonatal care and different healthcare systems, we are looking to include hospitals from 20 countries and if possible multiple hospitals of different neonatal care levels per country. Ideally, this would mean 4 hospitals per country, one per level of neonatal care. Participating hospitals will be recruited *via* direct contact, referrals by other hospitals and presentation of the study protocol at scientific congresses.

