## Discussion

Supporting postnatal transition of neonates seems to be the most frequently performed medical intervention (3). National and international guidelines are regularly updated in order to recommend an evidence based approach towards neonatal life support (17). However, data on the frequency of different interventions is scarce, outdated and often localized and therefore not representative for different health care systems or levels of care.

This international and multi-centre survey will provide much needed data on the frequency with which interventions are currently applied in the DR. Furthermore, the survey will examine the influence of different factors on administered interventions. Thereby, it will not only provide up-to-date information for future guidelines but will also help to generate hypotheses for further research and designing future studies on DR-management.

Current guidelines recommend different interventions in order to support postnatal transition, with a special focus on respiratory support (17). As a result, non-invasive positive pressure ventilation is a relatively common intervention with described frequencies ranging from 4% to 12% of all neonates (14, 18). Other interventions like the administration of chest compressions or epinephrine are much rarer at described frequencies from 0.1% up to 0.3% (3, 18) and 0.05% to 0.3% (14, 19) respectively. However, little is known for other interventions.

Video recordings of neonatal resuscitation represent a possible solution to track performed interventions (20). By detailed analysis of video recordings, certain DR-interventions in preterm and term infants after c-section were previously described both for a single centre and as a comparison between different centres (21–23). However, this data is not representative for all infants.

The multi-centre and international approach of surveying current DR-management allows a comparison across centres of different sizes, levels of neonatal care and health care systems. The survey is easy to perform and not very time consuming, thus it is easy for hospitals to participate, ensuring large data sets. The prospectively planned stratification into different subgroups will provide detailed information for certain risk groups. Comparison of data from different countries will disclose variations that could be due differences in local guidelines, recommendations and practices.

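### The 40,000-birth floor gives an expected 20 adrenaline cases, not a minimum of 20, and the 4,000-infant target quoted elsewhere does not secure those births

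*Protocol article*

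**What the plan says.** The Sample size section of the protocol article calls the choice empirical but then gives a derivation. It takes adrenaline as the rarest intervention, "The rarest described intervention in the literature is the administration of epinephrine with a frequency of as low as 0.05"%, and states the aim: "we wanted to collect data on at least 20 infants receiving this intervention". From this it concludes that "the calculated total number of births during the study period must equal or exceed 40,000". The births are then turned into sites ("We expect at least 500 births per participating hospital during the study period, leading to a target of 80 participating hospitals") and, with an assumed intervention rate of 10%, into 4,000 treated infants.

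The other two places that state the target drop the births. The Abstract (Methods) says: "The targeted sample size is at least 4,000 neonates who receive interventions". Anticipated results expects that "the targeted sample size of at least 4,000 neonates receiving interventions will be collected within 1 year" of the first hospital's enrolment.

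Two further ranges matter. For the intervention rate, the Abstract cites about 5% to 15%, and the Introduction says "it is estimated that up to 16% of newborns receive supportive interventions in the delivery room". For adrenaline, the Discussion gives "0.05% to 0.3% (14, 19) respectively".

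**The concern.** There are two separate problems.

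1. Dividing the wanted number of cases by the rate gives the number of births at which that many cases are expected on average. The article presents the result as the number of births needed to have at least that many. At the rate used for planning, an average of 20 falls below 20 in nearly half of repetitions.

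2. The adrenaline aim depends on births, but the target in the Abstract and in Anticipated results is a count of treated infants. The two counts agree only at an intervention rate of exactly 10%, and the article itself cites rates on both sides of that. A reader who has only the Abstract would judge completion by a count that does not settle whether the birth requirement was met.

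At stake is the only stated rationale for the size of the survey, and which count shows that the survey is complete.

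**Working it through.** **Inputs**
- Adrenaline planning rate: 0.05% (Sample size). Cited range: 0.05% to 0.3% (Discussion).
- Wanted adrenaline cases: at least 20. Births: at least 40,000. Births per hospital: at least 500. Assumed intervention rate: 10% (all Sample size).
- Cited intervention rates: 5% to 15% (Abstract), up to 16% (Introduction).

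**Step 1: the article's own figures.** All three reproduce exactly.
- 20 / 0.0005 = 40,000 births
- 40,000 / 500 = 80 hospitals
- 40,000 × 0.10 = 4,000 treated infants

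**Step 2: the chance of 20 or more adrenaline cases at 40,000 births.** Let X be the number of cases, X ~ Binomial(40,000, p). This treats births as independent with one common rate.

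| True rate p | Expected cases | P(X ≥ 20) |
|---|---|---|
| 0.05% | 20 | 0.530 |
| 0.065% | 26 | 0.90 |
| 0.1% | 40 | 0.9998 |
| 0.3% | 120 | about 1 |

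At 0.05% the 2.5th and 97.5th percentiles of X are 12 and 29, and the chance of falling short of 20 is 1 − 0.530 = 0.470. A Poisson calculation also gives 0.530. If exactly 20 cases were seen in 40,000 births, the exact (Clopper-Pearson) 95% interval for the rate would be 0.031% to 0.077%.

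**Step 3: variation between hospitals.** The common rate is a simplification. I let the rates of 80 hospitals of 500 births vary around 0.05% by a gamma distribution, with an assumed coefficient of variation of 0.5 or 1.0; the article gives no figure. In simulation the chance of 20 or more was 0.53 and 0.52, and the 95% range widened to 12–30 and 11–31. The conclusion does not depend on the simplification, but the range of 12 to 29 is the narrow case.

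**Step 4: births at which 4,000 treated infants are reached.** Births = 4,000 / intervention rate, with adrenaline at 0.05%.

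| Intervention rate | Births for 4,000 treated | Expected adrenaline cases | P(≥ 20) | Treated infants in 40,000 births |
|---|---|---|---|---|
| 5% | 80,000 | 40 | 0.9998 | 2,000 |
| 10% | 40,000 | 20 | 0.53 | 4,000 |
| 15% | 26,667 | 13.3 | 0.05 | 6,000 |
| 16% | 25,000 | 12.5 | 0.03 | 6,400 |

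The 15% and 16% rows combine the highest cited intervention rates with the lowest cited adrenaline rate. At 0.3%, 25,000 births would still give 75 expected cases and P about 1.

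**Step 5: births that would assure 20 or more at 0.05%.** The smallest N with P(X ≥ 20) at the chosen level is 47,267 for 80%, 51,802 for 90% and 55,755 for 95%. These levels are assumptions for scale, since the article states none.

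**The case against.** The strongest case on the other side has four parts.

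- **The planning rate is conservative.** 0.05% is the lowest of the cited values, and 40,000 births and 500 per hospital are both stated as minimums. At 0.1% the aim is practically certain. This stands, and it limits the first problem to true rates near the floor. It does not rescue the wording, because the floor is the rate from which the article derives its number.

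- **No assurance was promised.** The size is called empirical, the survey is largely descriptive, and no test or decision rule uses the figure of 20. This stands too, and is why the remedy is wording and not more births. But the section does set a criterion and presents 40,000 as following from it, and that step does not hold.

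- **The 10% conversion is disclosed as an assumption**, and it is the midpoint of 5% to 15%. That is fair. The conversion is not an arithmetic error. The weakness is that only the converted figure, without the assumption or the births, appears as the target elsewhere.

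- **Nothing says the survey stops at 4,000 treated infants.** This is also correct. A reader might infer from Step 4 that the survey can close at about 25,000 births with a 3% to 5% chance of reaching 20 adrenaline cases. The documents do not support that. The Sample size section separately requires 40,000 births and targets 80 hospitals, each hospital collects for a fixed six months, and monthly births are recorded at every site, so the requirement can be tracked. The 3% and 5% figures apply only if the Abstract and Anticipated results are read without the Sample size section.

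**Conclusion.** The point holds in a limited form.

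At the article's own planning rate, 40,000 births give 20 expected adrenaline cases and a 53% chance of 20 or more. This rests on independent births with a common rate; variation between hospitals widens the range of 12 to 29 and barely moves the 53%. It would be too strong to say that the design fails its adrenaline aim: the chance is already 0.90 at about 0.065%, within the range the article cites.

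The treated-infant target in the Abstract and Anticipated results does not by itself secure the birth requirement. At the cited 15% to 16% it is met at about 25,000 to 26,700 births. At 5% the mismatch runs the other way: the required births produce half the stated number of treated infants. This is an inconsistency about which count defines completion, not evidence that recruitment will end early.

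**What to change.** - In the Abstract, Sample size and Anticipated results, state at least 40,000 births as the target that defines completion. The monthly birth counts already collected from each site are enough to monitor it.
- Give 4,000 treated infants as a projection at 10%, with the range 2,000 to 6,400 for intervention rates of 5% to 16%.
- In Sample size, replace the minimum of 20 by wording such as: an expected 20 adrenaline cases at 0.05% (about 12 to 29; 53% chance of 20 or more), more if the rate is higher. Note that the range assumes a common rate across hospitals.

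This changes wording only. No hospitals, data items or analyses are added. The cost is a slightly less favourable stated figure. If the study team prefers to keep 20 as a true minimum at 0.05%, it would have to choose an assurance level and raise the birth target, to about 47,300 for 80% or 51,800 for 90%. At 500 births each, that is about 95 or 104 hospitals instead of 80.
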